### Sample size calculation

Taking data in the scientific literature on the rate of vaginal delivery within 24 h after the administration of the study drugs (70% for oral misoprostol [12], 55% for dinoprostone [12] and 54% of vaginal misoprostol [24]) as a reference, we will need to analyse 333 women (111 per arm) to detect significant differences between the groups with a power of 90% and a confidence level of 95%. Assuming a 10% rate of losses during the follow-up period, we will therefore need to recruit a total of 372 women (124 per arm).

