### Variables

The data collected will be recorded on case report forms, safeguarding patient confidentiality at all times. The primary outcome will be the rate of vaginal delivery (normal or instrumental) within the first 24 h after drug administration.

The secondary outcomes include cervical status (Bishop score of 6 or over, assessed 12 and 24 h after drug administration), percentage of caesarean sections, use of oxytocin and, if so, the total dose, duration of latent and active phases and the pushing stage of labour, induction failure (no progress into the active phase of labour after administering oxytocin for 12 ± 3 h after membrane rupture), uterine tachysystole, hypertonicity, hyperstimulation, or rupture, adverse events including maternal and/or foetal death, pain (assessed on a visual analogue scale), women’s satisfaction with the induction process (assessed using a dichotomous question, asked 2 days after childbirth or on hospital discharge), maternal morbidity (uterine rupture, severe postpartum haemorrhage or intensive care unit admission) and foetal morbidity (1- and 5-min APGAR scores, umbilical cord pH, and neonatal asphyxia, among other variables).

Due to the extensive information about misoprostol and dinoprostone in the literature, it was considered that a data monitoring committee was not needed. We report to the ethics committees yearly on the progress of the trial. Currently, we have no plans to make any major modifications to the protocol, but we will communicate any such modifications to all people involved.

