### Statistical analysis

First, we will describe the general characteristics of the sample. For this, percentages with 95% confidence intervals will be calculated for qualitative data and means and standard deviations for quantitative data.

Second, logistic regression analysis will be used to assess the relationship between the intervention received and the primary outcome (vaginal delivery within the first 24 h after administration of the corresponding drug). Crude and adjusted models will be constructed using variables found to be confounding factors in the univariate analysis.

Logistic regression analysis will also be used to analyse the rates of vaginal deliveries at 12 and 48 h after starting induction and the ripening of the cervix at 12 and 24 h. The rates of maternal adverse events (gastrointestinal adverse effects, uterine tachysystole, uterine rupture, uterine hyperstimulation, morbidity, postpartum haemorrhage, and fever) and of caesarean sections will be compared between the groups with a chi-square test.

Third, multiple linear regression analysis will be performed to explore the relationships between duration of the labour (total, and of active and latent phases), the maximum level of pain reported by the woman, 1- and 5-min APGAR scores, umbilical cord pH, and the intervention (vaginal dinoprostone, and oral or vaginal misoprostol). As well as crude models, adjusted models will be built controlling for intervention group. Complications and adverse events including neonatal asphyxia, morbidity, neonatal intensive care unit admission, and mortality and other complications will be compared between groups with a chi-square test.

Both intention-to-treat and per-protocol analysis will be performed. For the intention-to-treat analysis, we will consider all women included in the study who received at least one dose of any medicine. To handle any missing data on satisfaction, we will use multiple imputation techniques, taking into account age, parity and other potentially relevant variables. We will use the IBM SPSS Statistics for Windows, version 22.0, considering a *p* value of < 0.05 to be significant.

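### Ripening at 12 and 24 h has no scoring rule for women who deliver or have a caesarean first, and linear regression of labour durations cannot accommodate labours cut short by caesarean

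*Protocol article*

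**What the plan says.** In the protocol article, the Variables section lists as a secondary outcome "cervical status (Bishop score of 6 or over, assessed 12 and 24 h after drug administration". The Statistical analysis section puts "the ripening of the cervix at 12 and 24 h" into logistic regression. The same section uses multiple linear regression to "explore the relationships between duration of the labour (total, and of active and latent phases", among other outcomes.

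The intention-to-treat set is every included woman given one dose or more. The one rule for missing values reads: "To handle any missing data on satisfaction, we will use multiple imputation techniques".

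Two other statements matter. The Procedure section sends women whose induction fails to caesarean. The Variables section defines induction failure as not reaching the active phase despite oxytocin. The article therefore expects some labours in which a phase is never completed.

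**The concern.** A woman who has delivered has no Bishop score. The primary outcome is vaginal delivery within 24 h, so the women who cannot be scored at 24 h are mainly the primary outcome's successes, and the arms are expected to differ in how many there are. If the unscored women drop out of the logistic model, what is left is not a comparison of randomised groups: the more effective drug keeps a smaller remnant, richer in slow responders.

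The duration models have a related problem. A caesarean before the active phase leaves an uncompleted latent phase and no active phase. A caesarean during active labour leaves a truncated active phase. In either case the total duration ends at surgery, not at vaginal birth. Ordinary linear regression has no valid value to enter: the woman is either omitted or given a time that is too short. Failed inductions are by definition among the slowest labours.

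At stake is the reading of the ripening and labour-duration results. The article's Discussion looks to oral misoprostol as a possible first choice in women with an unfavourable cervix, and ripening bears directly on that.

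**Working it through.** **Inputs.** From Sample size calculation: vaginal delivery by 24 h of 70% (oral), 55% (dinoprostone) and 54% (vaginal misoprostol); 111 analysed per arm. The step from analysed to recruited reproduces: 111/0.9 = 123.3, rounded up to 124 per arm, or 372. The power claimed for 111 is a separate matter; here 111 serves only as a denominator.

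**1. Women who can have a 24-h score.** Share = 1 − share delivered.

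| Arm | Share undelivered | Of 111 |
|---|---|---|
| Oral misoprostol | 1 − 0.70 = 0.30 | 33.3 |
| Dinoprostone | 1 − 0.55 = 0.45 | 50.0 |
| Vaginal misoprostol | 1 − 0.54 = 0.46 | 51.1 |

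These are upper limits, because caesareans before 24 h remove more. If 5% or 10% of each arm had a caesarean by then (assumed), the counts would be about 28/44/46 or 22/39/40.

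**2. The 12-h score.** The Background cites a study with 48.5% (vaginal misoprostol) and 13.3% (dinoprostone) delivered vaginally by 12 h. Applied here as an illustration, that leaves 51.5% and 86.7%, or 57 and 96 of 111.

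**3. Direction of the distortion at 24 h.** Let d be the share delivered and r the share ripened among all women, with delivered women counted as ripened and caesareans ignored. Among the undelivered, the unripened share is (1 − r)/(1 − d). For oral against dinoprostone, scoring only the undelivered therefore multiplies the ratio of unripened shares by 0.45/0.30 = 1.5. An advantage for oral (ratio below 1) is weakened. It reverses if the ratio in all women lies between 1/1.5 = 0.67 and 1, that is, if oral reduces the unripened share by less than a third.

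Illustrations, with assumed ripening values:

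- Equal ripening of 90% in both arms: (0.90 − 0.70)/0.30 = 67% against (0.90 − 0.55)/0.45 = 78%. At 80% the figures are 33% and 56%; at 95%, 83% and 89%. A true null appears as a deficit for oral of 6 to 22 percentage points.
- Ripe among the undelivered 30% (oral) and 40% (dinoprostone): in all women, 0.70 + 0.30 × 0.30 = 79% and 0.55 + 0.45 × 0.40 = 73%, odds ratio 1.39 for oral. Among the undelivered, (0.30/0.70)/(0.40/0.60) = 0.64.

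**4. Simulation, oral against dinoprostone.** Log-normal ripening times and ripening-to-delivery lags were assumed and calibrated to 70% and 55% delivered by 24 h. Odds ratios for ripening, favouring oral when above 1:

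| Scenario | All women | Undelivered only |
|---|---|---|
| 24 h, no non-responders | 2.04–3.09 | 1.45–2.16 |
| 24 h, 20% non-responders in both arms | 1.15–1.65 | 0.49–0.78 |
| 12 h, all scenarios | 1.94–2.63 | 1.70–2.23 |

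The advantage is weakened throughout. It reverses only at 24 h, and only with the assumed non-responders.

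**5. Durations.** The article gives no durations, standard deviations or expected caesarean rates for its own population, so no bias can be calculated.

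**The case against.** The strongest objection is that the article never says ripening is analysed only in women with a score. It names a yes/no outcome, a logistic model and an intention-to-treat set, and nothing prevents counting a delivered woman as ripened. An article condenses, and a scoring rule could sit in the full protocol or analysis plan, which are not shown. This stands against reading the text as a decision to restrict the analysis. It does not remove the difficulty: the outcome is fixed as a score at set times, it cannot be obtained in more than half of each arm at 24 h, and the one stated rule for missing values covers satisfaction. For durations the objection is weaker, because linear regression is named outright.

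Three further inferences go beyond the document:

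- **That the faster drug will look worse.** Weakening is the general result. Reversal depends on assumptions, and no simulated scenario showed it at 12 h.
- **That the caesarean rates cited in the Background (20% dinoprostone, 11% vaginal misoprostol) measure the missing durations.** They come from a retrospective study of women with ruptured membranes, whereas this trial requires intact membranes. Nor does every caesarean lose every duration: surgery in active labour leaves a complete latent phase.
- **That the comparison of speed is lost.** Vaginal delivery at 12, 24 and 48 h is also analysed and is definable for every woman, caesarean rates are compared separately, and the duration models are described as exploratory. This limits the consequence.

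**Conclusion.** The point holds for secondary outcomes and should be corrected. As worded, ripening at 24 h is measurable in at most about 30%, 45% and 46% of the arms if the plan's own delivery rates hold, and no rule covers the other women. A scored-women-only analysis would be selective by arm. For oral against dinoprostone it would multiply the ratio of unripened shares by 1.5, ignoring caesareans. That generally shrinks the faster drug's advantage and, under some assumptions at 24 h, reverses it. That such an analysis would be run is an inference from silence, not something the article states.

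For durations, the chosen model does not suit labours that caesarean ends early. The direction and size of that bias cannot be established from the document. The primary outcome is defined for every woman and is unaffected.

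**What to change.** - **Ripening.** In the intention-to-treat set, count a woman as ripened by 12 or 24 h if by then she had a Bishop score of at least 6, or active labour as Table 1 defines it, or a vaginal delivery. Count a caesarean before ripening as not ripened. The logistic model can then stay.
- **Durations.** Compare time from first dose to active labour, and to vaginal delivery, by cumulative incidence with caesarean as a competing event (for example Gray's test or a Fine-Gray model). Report durations among vaginal births descriptively or as supportive only.

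The cost is a change of wording, recording the time of caesarean if it is not already captured (the article lists the caesarean percentage but not its timing), and software beyond SPSS 22 for the competing-risk analysis. The sample size and the primary analysis do not change.

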Loss of UA after optimal UA	- **When “off” drug:** respect the period of rest and restart with dose depending on the previous level of UA (following the 3 + 1 regimen) (Example 3) - **When “on” drug**: increase the dose and follow the 3 + 1 regimen (Example 4)	Maintain regimen	Confirm the presence of the drug in vagina:
			- Lack of drug: administer additional dose. - Presence: maintain regimen.
Active labour + loss of UA after optimal UA		When in combination with a lack of progression of labour, STOP treatment + oxytocin protocol	
Active labour + no progress	STOP treatment + oxytocin protocol		
Non-reassuring cardiotocographic pattern	STOP treatment + oxytocin protocol		
Uterine tachysystole or hypertonicity	STOP treatment (if later UA falls below optimal levels, restart treatment with a lower dose than before the episode of hyperstimulation) (Example 5)	STOP treatment (if later UA falls below optimal levels, restart treatment)	STOP treatment (if later UA falls below optimal levels, start oxytocin protocol)
End of treatment without UA	Oxytocin protocol		
End of treatment with UA	Watchful waiting + oxytocin protocol if loss of UA		

Optimal UA: at least 3 contractions lasting more than 60 s every 10 min

Little UA: less than 3 contractions every 10 min

Active labour: at least 4 cm of dilatation with optimal UA

No progress of labour: The following criteria must be met:

- Latent phase of labour completed and active phase of labour started (cervical dilation of 4 cm or more)

- Contraction pattern of 3 contractions every 10 min with adequate intensity for 4 h without cervical changes

Non-reassuring cardiotocographic trace:

- Recurrent late decelerations lasting for 30 min or more

- Atypical variable decelerations in more than 50% of the contractions for 30 min or more

- Prolonged decelerations: decrease in foetal heart rate (FHR) by ≥15 beats per minute (bpm) for 2 to 10 min

- Foetal bradycardia: FHR < 100 bpm for more than 10 min

- Reduction in variability indicating a need for intervention

- Sinusoidal FHR pattern

Uterine tachysystole: Six or more contractions in 10 min for at least 30 min

Hypertonicity: Sustained uterine contractions for more than 2 min without complete uterine relaxation

Uterine hyperstimulation: Excessive uterine activity with abnormal FHR

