**Table 2 Tab2:**
[figure not shown]
Schedule of enrolment, interventions, and assessments during the clinical trial

Additionally, in all of the groups, in the event that the maximum treatment period is completed without adequate uterine response, women will start to be given oxytocin for a maximum period of 24 h. If delivery is achieved by the end of this period, the induction will be considered a success. If induction is unsuccessful, a caesarean section will be performed.

Oxytocin infusion protocol: First, 10 units of oxytocin will be added to 500 ml of saline. The rate of infusion will be set at 3 ml/hour, doubling the dose every 20 min up to 24 ml/hour (yielding doses of 3, 6, 12 and 24 ml/h). Subsequently, the dose will be increased by 6 ml/hour every 20 min up to 120 ml/h. If uterine activity is still inadequate with this dose, 20 units of oxytocin in 500 ml of saline will be used with a starting rate of 60 ml/hour increasing the dose by 3 ml/hour every 20 min up to a dose of 90 ml/hour.

The women and their infants will be followed-up until discharge from hospital.

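### Caesarean section is assigned an unadjusted between-group chi-square test, which gives no pairwise estimate or interval, while the other delivery outcomes get logistic regression (minor, free improvement)

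*Protocol article*

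**What the plan says.** All the analysis statements below come from Methods/design, Statistical analysis, in the protocol article.

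- **Primary outcome (vaginal delivery within 24 h):** logistic regression, followed directly by "Crude and adjusted models will be constructed using variables found to be confounding factors in the univariate analysis".
- **Vaginal delivery at 12 and 48 h:** "Logistic regression analysis will also be used to analyse the rates of vaginal deliveries at 12 and 48 h after starting induction". This sentence does not say whether the models are crude, adjusted or both.
- **Caesarean section:** grouped with the maternal adverse events, whose rates "and of caesarean sections will be compared between the groups with a chi-square test". No effect measure, between-arm interval or pairwise contrast is named.
- **Intervals:** mentioned once, for describing the sample: "percentages with 95% confidence intervals will be calculated for qualitative data".

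The Variables section lists "percentage of caesarean sections" among the secondary outcomes. A lower caesarean rate with oral misoprostol appears as rationale in the Abstract, in the Background (Oral misoprostol) and in the Discussion.

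The Procedure section (text after Table 2) says that when the maximum treatment period ends without adequate uterine response, "women will start to be given oxytocin for a maximum period of 24 h", and then: "If induction is unsuccessful, a caesarean section will be performed". Table 1 adds a separate path for women who finish treatment with uterine activity: "Watchful waiting + oxytocin protocol if loss of UA".

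**The concern.** The caesarean questions raised in the document are pairwise: oral misoprostol against vaginal dinoprostone, and oral against vaginal misoprostol. A chi-square comparison across three groups does not say which arms differ or by how much. If the result is not significant, a reader has only a p-value and may take it as evidence of no difference.

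The choice also sits oddly beside its neighbours. Three closely related binary delivery outcomes are modelled, and caesarean section is not. Parity and Bishop score have to be established before randomisation, because the eligibility criteria limit both, yet they play no part in the caesarean analysis. At stake is how informative one secondary result will be, not whether its test is valid.

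**Working it through.** **1. Is there a plan figure to reproduce?** The article gives no power or precision figure for caesarean section. The arm sizes used here are its own: 111 per arm analysed and 124 per arm recruited, and 111 / 0.9 = 123.3, rounded up to 124, agrees.

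**2. Illustrative rates.** The Background (Vaginal misoprostol) quotes caesarean rates of 20% with dinoprostone and 11% with vaginal misoprostol. They come from a retrospective study of women with ruptured membranes. This trial requires intact membranes, and that study had no oral arm. The rates serve only to show the scale.

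**3. Precision of one pairwise difference.** Half-width = 1.96 × √[(0.20 × 0.80 + 0.11 × 0.89) / n] = 1.96 × √(0.2579 / n).

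| n per arm | Half-width (points) | Risk difference, 95% CI (points) | Odds ratio, 95% CI |
|---|---|---|---|
| 111 | 9.4 | 9.0 (-0.4 to 18.4) | 0.49 (0.23 to 1.05) |
| 124 | 8.9 | 9.0 (0.1 to 17.9) | 0.49 (0.24 to 1.01) |

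**4. Power of one pairwise test** (two-sided 5%; sidedness is not stated, so this is assumed). With mean rate 0.155, power = Φ{[0.09 − 1.96 × √(2 × 0.155 × 0.845 / n)] / √(0.2579 / n)}. This gives 46% at n = 111 and 50% at n = 124.

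**5. Power of the three-group test** (2 df, noncentral chi-square), with the third arm assumed:

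| Rates in the three arms | 111 per arm | 124 per arm |
|---|---|---|
| 20%, 15.5%, 11% | 36% | 40% |
| 20%, 20%, 11% | 44% | 48% |
| 20%, 11%, 11% | 50% | 55% |

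So even if a 9-point difference were real, a non-significant result would be about as likely as not, or more likely.

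**6. Does the choice of test itself change the answer?** Take 25, 20 and 14 caesareans among 124 women per arm. Chi-square is 3.67, p = 0.160. The complementary counts (99, 104, 110) give the same value. The likelihood-ratio test of a crude logistic model gives 3.73, p = 0.155. Over 20,000 simulated trials at each arm size (rates 20%, 15.5%, 11%), the two tests reached the same 5% decision in about 98% of trials, and their p-values differed by at most 0.03. Without covariates they are practically the same test. What the model adds is the estimate, the interval and the option to adjust.

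**7. What would adjustment gain?** The share of variance removed by parity = q(1 − q)(c_n − c_p)² / [p(1 − p)], where q is the nulliparous share, c_n and c_p are the caesarean rates in nulliparous and parous women, and p is the overall rate. None of these is in the document; all are assumed.

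- q = 0.65, rates 22% and 6%: 4.2%
- q = 0.65, rates 25% and 5%: 6.2%
- q = 0.50, rates 25% and 5%: 7.8%

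At 111 per arm, multiplying 9.4 points by √(1 − 0.042) to √(1 − 0.078) gives roughly 9.1 to 9.2 points.

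**8. How close is 48 h vaginal delivery to the complement of caesarean section?** Up to 24 h of drug plus up to 24 h of oxytocin is 48 h, after which an unsuccessful induction ends in caesarean section. That makes the two roughly complementary. Because women with uterine activity at the end of treatment may be observed first, some vaginal births after 48 h are possible. The document gives no proportion.

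**The case against.** The strongest reply is that nothing here is an error. An unadjusted chi-square test of a binary secondary outcome is valid under 1:1:1 randomisation, and adjustment is optional. Effect measures and contrasts for secondary outcomes are commonly left to an analysis plan, which is not shown. The wording does not rule out pairwise chi-square tests, and arm percentages, from which differences follow, will presumably be reported. Low power for a secondary outcome comes from the sample size, not the test. Nor is caesarean rate the only rationale: the Background also cites tolerability, hyperstimulation and delivery within 24 h.

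Most of this stands, and it sets the severity. It does not remove the point, because the article does more than stay silent: it names a method for caesarean section that differs from the one for the other delivery outcomes. Even pairwise chi-square tests would give no estimate or interval.

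A reader might go further and infer that one result is being tested twice by conflicting methods, with crude and adjusted models at 48 h but not for caesarean section. The document does not support that. Adjusted models are explicit only for the 24 h primary outcome; extending them to 48 h rests on the word for also. The crude logistic and chi-square tests practically coincide, so disagreement could come only from adjustment or from vaginal births after 48 h. And 48 h delivery is not in the Variables list, so nothing shows that it would be counted as separate support.

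**Conclusion.** The point holds as a minor matter of analysis choice and reporting. The stated method for caesarean section is valid but less informative than the one already planned for the other delivery outcomes, and it leaves two known baseline variables unused.

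On the illustrative rates, a pairwise difference would be known to within about 9 points either way, with pairwise power of about 46 to 50%, so a p-value alone would say little. These figures rest on rates from a different population and on a two-sided 5% test. They show why an interval is needed, not what this trial will find. The gain from adjusting for parity, a few tenths of a point in half-width, is modest and depends wholly on assumed rates. It should not be presented as correcting a bias.

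**What to change.** In the analysis plan, move caesarean section out of the adverse-event list and analyse it with a logistic model containing randomised arm, parity and baseline Bishop score, with these covariates fixed in advance. From that model, report the risk difference with 95% confidence interval for each pair of arms, for example by averaging predicted risks over all analysed women under each arm, with a delta-method or bootstrap interval. If that is awkward in the named software, unadjusted pairwise risk differences with 95% intervals already supply most of what is missing.

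Keep chi-square, or an exact test where counts are small, for the rare adverse events. When reporting, note that vaginal delivery by 48 h is roughly, not exactly, the complement of caesarean section, so that the two are not read as independent support.

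Cost: a few lines of analysis wording and one more model. No new data, and no change to the sample size or to trial conduct.

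### Apgar score and cord pH have linear regression as their only stated analysis, so a low-tail excess of depressed or acidotic newborns is summarised as a small mean difference

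*Protocol article*

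**What the plan says.** The Variables section lists, among the secondary outcomes, "foetal morbidity (1- and 5-min APGAR scores, umbilical cord pH, and neonatal asphyxia, among other variables". It gives no threshold for any of them.

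The Statistical analysis section states that "multiple linear regression analysis will be performed to explore the relationships between duration of the labour". The same sentence continues to maximum pain, "1- and 5-min APGAR scores, umbilical cord pH, and the intervention (vaginal dinoprostone, and oral or vaginal misoprostol". Crude and adjusted models are planned. The section states no cut-off, proportion or ordinal method for Apgar or pH.

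Other neonatal outcomes in that section are handled as rates: "neonatal asphyxia, morbidity, neonatal intensive care unit admission, and mortality and other complications will be compared between groups with a chi-square test". Neither asphyxia nor morbidity is defined there.

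**The concern.** A linear regression coefficient for treatment is a difference in means. The Apgar score is a bounded, ordinal score from 0 to 10, and most term newborns can be expected near the top. For both Apgar and cord pH, the newborns who matter for safety are the few at the low end. The mean averages them with a large healthy majority, so a several-fold excess of low values appears as a fraction of an Apgar point or about a hundredth of a pH unit. Neither figure tells a reader how many more newborns were depressed or acidotic.

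This matters because the Background names excess uterine activity, with or without cardiotocographic abnormalities, as the main adverse effect of these drugs, and the Discussion expects to draw conclusions about safety as well as efficacy. The plan already treats another score by threshold: Bishop score is dichotomised at 6 and analysed by logistic regression.

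**Working it through.** **Inputs from the document.** The plan has no power figure for Apgar or pH, so there is none to reproduce. Its sample size supplies only the number per arm: "we will need to analyse 333 women (111 per arm) to detect significant differences between the groups with a power of 90"%, and after losses 111 / 0.9 = 123.3, rounded up to 124 per arm, or 372 in total, which agrees with the text. (The 111 does not itself follow from the stated rates at 90% power: the two-sided two-proportion formula gives 217 per arm for 70% vs 55% and 192 for 70% vs 54%. That is a separate matter, on which this point does not depend.)

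**Assumptions.** The document gives no Apgar or pH distribution, so the following are illustrative. The cut-offs of 7 and 7.10 serve the arithmetic only. Tests are two-sided at 0.05, and the regression contrast between two arms is taken as a two-sample t-test.

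**5-minute Apgar.** Assumed probabilities for scores 3 to 10 are .001, .001, .003, .005, .02, .05, .42, .50. The mean is 9.372, the SD 0.80, and 1% score below 7.
- Mean of scores below 7: (.003 + .004 + .015 + .030) / .01 = 5.20. Mean of the rest: (9.372 − .052) / .99 = 9.414. Each newborn moved into the low group costs 4.214 points on average.
- Low share 1% to 5%: mean difference .04 × 4.214 = 0.169 (SD in the worse arm 1.15).
- Low share 1% to 8%: mean difference .07 × 4.214 = 0.295 (SD in the worse arm 1.35).
- Hand check, 1% vs 8%, 124 per arm: SE = √[(0.80² + 1.35²)/124] = 0.141; 0.295/0.141 = 2.09; power ≈ Φ(2.09 − 1.96) = 55%.

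| Scenario | Mean (t-test) | Fisher, share below 7 | Chi-square, share below 7 |
|---|---|---|---|
| 1% vs 5%, 111 per arm | 22% | 23% | 41% |
| 1% vs 8%, 124 per arm | 57% | 70% | 80% |

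These are simulated; repeat runs differ by one or two points.

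**Cord pH.** Assumed mixture of N(7.26, 0.07) and an acidotic group N(7.05, 0.05), with the acidotic share rising from 2% to 8%.
- Mean difference: .06 × (7.26 − 7.05) = 0.0126.
- Variances: .98(.0049) + .02(.0025) + .02(.98)(.21²) = .00572, and .92(.0049) + .08(.0025) + .08(.92)(.21²) = .00795.
- At 111 per arm, SE = √(.01367/111) = 0.0111; 0.0126/0.0111 = 1.14; power ≈ Φ(1.14 − 1.96) = 21%.
- Simulated power at 111 to 124 per arm: mean about 21%, chi-square on the share below 7.10 about 38–41%, Fisher 28–30%.
- If the two groups are instead separated exactly at 7.10 (acidotic SD 0.04, 111 per arm), the figures are 20% for the mean and 54% for chi-square.

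**Would an ordinal model do better?** With only the low tail growing from 1% to 8% at 124 per arm, a rank test has 18% power, and a fitted proportional-odds model 19% (200 trials), against 57% for the mean. For a general downward shift (odds ratio 1.8) the order reverses: rank test 67%, mean 59%.

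The probabilities .005, .005, .015, .025, .02, .05, .228, .652 also have mean 9.372, but 5% score below 7. Compared with the first distribution at 124 per arm, the expected mean difference is zero. The rank test is significant in 45% of trials, always in favour of the arm with more low scores; the proportional-odds model is significant in 37% of 200 trials, in the same direction.

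**The case against.** The strongest reply is that harm is already compared as rates. Asphyxia, morbidity, intensive care admission and mortality all go to a chi-square test, so an excess can show there. This stands against any inference that foetal harm is judged only on means, or that Apgar and pH are the only measures of it; the document does not support that reading. One could also argue that Apgar and pH, being listed under foetal morbidity, would be categorised within the morbidity comparison. The text neither says so nor rules it out.

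Second, the power gain is modest and depends on the test. For 1% vs 5% at 111 per arm, Fisher's test gains almost nothing over the mean (23% vs 22%). This stands. The firmer argument is interpretability: a risk difference with its interval shows what excess is excluded, and a shift of 0.013 pH units does not.

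Third, a reader might infer that linear regression should give way to a proportional-odds model because Apgar is ordinal. The figures above do not support this for a low-tail excess. The equal-mean example only shows what is possible, since nothing in the document suggests that a drug would act in that way.

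Fourth, cut-offs are commonly left to a full protocol or analysis plan, and these are secondary outcomes in models described as exploratory. Missing cut-offs are therefore not the point; the point is that the article names one method for these outcomes and that it yields means. For cord pH, a continuous measure, the mean difference is valid, but it answers a different question from the safety one.

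**Conclusion.** The point holds in a limited form. Two of the listed foetal morbidity measures have a mean comparison as their only stated analysis, and at this sample size it often misses a several-fold excess of low values: detection is about 22–57% for Apgar and about 21% for pH, against about 41–80% and 38–41% with a chi-square test on the proportion. These figures rest on assumed distributions, assumed cut-offs and two-sided tests at 0.05; with Fisher's test the advantage shrinks to 23–70% and 28–30%. Power for rare events stays limited under either approach. The primary outcome and the conduct of the trial are unaffected. The change is worth making because it is cheap and gives the safety conclusions a readable scale.

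**What to change.** In the Statistical analysis section, add a between-arm comparison, by randomised group, of the proportion with low 5-minute Apgar and the proportion with low cord pH. Report risk differences with 95% confidence intervals, at cut-offs that the neonatal team fixes before analysis. Name these as the main safety summaries of the two measures and keep the linear-regression mean differences as supplementary. State whether the morbidity and asphyxia comparisons include low Apgar or low pH. An ordinal Apgar model may be added as a complement, but should not be the main analysis.

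The cost is a few lines of text and a few extra runs on data already to be collected. The small downside is two more secondary comparisons. Because events will be few, interpretation should rest on the confidence intervals and not on whether p falls below 0.05.
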